## Abstract

**Introduction:**

Psoriasis vulgaris is a common skin disease characterized by persistent localized erythematous scaly plaques, typically on the elbows, knees, and scalp. It is an immune-abnormal disease that progresses slowly over a long period with frequent symptom recurrence. Current studies have shown that acupuncture is an effective therapy for psoriasis. However, the scientific evidence of the efficacy of auricular acupressure treatment for patients with psoriasis is still insufficient. Therefore, we designed a randomized controlled clinical trial to investigate the effect, safety, and cost-effectiveness of auricular acupressure in addition to medication in patients with psoriasis.

**Methods and analysis:**

This on-going study is a two-arm parallel, assessor-blinded, randomized controlled trial in which 180 participants with psoriasis will be recruited and then randomly allocated into two groups in a 1:1 ratio. Equal randomization will be conducted using a computer-generated random allocation sequence. Participants in the intervention group will receive auricular acupressure treatment once per week for 4 weeks, and calcipotriol betamethasone ointment for topical use once daily for 4 weeks. Participants in the control group will receive only calcipotriol betamethasone ointment treatment once daily for 4 weeks. All patients will be followed up for 12 weeks. The primary outcome is relapse rate. The secondary outcomes include time to relapse, rebound rate, time to new onset, Psoriasis Area and Severity Index score improvement rate, body surface area affected, a visual analogue scale, and Dermatology Life Quality Index. Cost-effectiveness analysis will be carried out from a health and community care provider perspective.

**Discussion:**

This multicenter randomized controlled trial will provide important clinical evidence for the effect and safety of auricular acupressure as a complementary therapy in patients with psoriasis.

**Trial registration:**

Chinese Clinical Trial Registry, ChiCTR-TRC-14004916. Registered on 20 May 2014. This protocol is version 3.0 which was updated on 24 September 2016.

**Electronic supplementary material:**

The online version of this article (10.1186/s13063-019-3475-4) contains supplementary material, which is available to authorized users.

## Background

Psoriasis vulgaris is an immune-abnormal, chronic skin disease characterized by well-delineated red, scaly plaques. It is induced by a number of environmental factors and arouses great public concern because of its high prevalence, impact on life quality, and incurable characteristics [1]. With a prevalence of 1% to 3%, psoriasis is likely to be encountered by general practitioners [2]. Furthermore, psoriasis has also been associated with a significantly increased risk of myocardial infarction, stroke, and peripheral vascular disease, possibly because of accelerated atherosclerosis in the setting of an inflammatory state [3].

Traditional Chinese medicine (TCM) is based on the fundamental principle of Yin-Yang balance, Five Elements, and a relationship between humans and nature [4]. When treating diseases, TCM first evaluates presenting symptoms to differentiate the syndrome related to the disease and then clarifies a therapeutic method for this disease. For more than 2000 years, TCM has been used to treat various diseases in China and throughout East Asia, and it still remains the first choice of treatment for many people because its effectiveness and its cost being inexpensive. Clinical practices have also proved that TCM is beneficial and effective in alleviating clinical symptoms, improving quality of life, immune function, reducing metastasis, and preventing recurrence in various diseases [5–10].

In the perspective of TCM, the pathogenesis of psoriasis is deficiency in origin and excess in symptom (Ben Xu Biao Shi), and in most cases it co-occurs with blood stasis. In chronic psoriasis, *qi* was exhausted during a long disease course and then the blood circulation was disturbed. Finally, *qi* and blood coagulated and blocked the meridians, which led to lack of nourishment for the skin and muscle. Thus, TCM clinical experts advocated ‘treatment of psoriasis from the blood aspect’ [11, 12]. The effective ways to achieve this are blood-activating herbal medicines and treatments such as acupuncture and bloodletting. A systematic review indicated that the evidence for the effect of multi-herb formulations for psoriasis was promising in a number of the studies [13]. A meta-analysis reported that Chinese medicine was effective for psoriasis vulgaris since it is noninferior to acitretin and it could produce add-on effects when combined with acitretin, as well as reducing the acitretin-induced adverse events [14]. Chinese medicine combined with narrowband ultraviolet B for treating psoriasis also showed improved efficacy [15, 16]. Herbal formulae or plant extract topical management were analyzed in other systematic reviews, which showed that topical herbal formulae or plant extracts could improve overall clinical symptoms [17–19].

Acupuncture is a typical representative of TCM, and is one of the various general therapies for psoriasis. In a systematic review, acupuncture therapies show some evidence of benefit for the treatment of psoriasis [20]. Auricular acupressure is the acupuncture-related practice. It is a noninvasive form of acupuncture which uses physical pressure applied to the auricular acupressure point (AAP) by *Vaccaria* seeds [21]. The prescription component of auricular acupressure is principally based on the divisions of the auricle, with definite terms and denoting s [22]. Named AAPs and regions are distributed over the entire surface of the auricle (Fig. 1).

**Fig. 1 Fig1:**
[figure not shown]
Standard codes for the division of the auricle

Auricular acupressure is characterized by balancing Yin and Yang, dredging meridians and collaterals, regulating the functions of organs, and building up body resistance to pathogenic factors [23]. Auricular acupressure has been used to treat various diseases. In recent studies, auricular acupressure has been shown to help menstruating women effectively relieve menstrual headache [24]. Furthermore, it has been shown that auricular acupressure treatment can improve sleep quality and daytime dysfunction in insomnia patients [25–27]. By stimulating a point on the ear, a promising therapeutic effect is believed to occur on the gross anatomical organ associated with that point. Studies have demonstrated that auricular therapy can promote general *qi* and blood circulation; hence, it can eventually improve the blood flow [28].

Since there is little experience using auricular acupressure in psoriasis, we aim to analyze the additional efficacy on symptom improvement and relapse rate associated with auricular acupressure treatment for psoriasis. The aim of our study is to show whether there is additional benefit in improving symptoms and preventing recurrence when adding auricular acupressure treatments to usual therapy compared with usual therapy alone for people with psoriasis.

## Methods/design

### Study design

This study is a two-parallel arm, assessor-blinded, randomized controlled trial. The trial will be conducted by Guangdong Provincial Hospital of Chinese Medicine (GPHCM) and performed at two clinical research centers in China (Guangdong Provincial Hospital of Chinese Medicine and Guangzhou Red Cross Hospital) in accordance with the Declaration of Helsinki and the Guidelines for Good Clinical Practice.

This study will select patients with blood stasis syndrome on a TCM diagnosis based on a TCM syndrome differentiation standard [29, 30]. Eligible participants will be stratified by age and sex and randomly allocated in a 1:1 ratio to one of the treatment arms (the auricular acupressure plus calcipotriol betamethasone ointment group or the control calcipotriol betamethasone ointment group) and receive treatment for 4 weeks, with 12 weeks of follow-up (Fig. 2). The Standard Protocol Items: Recommendations for Interventional Trials (SPIRIT) checklist is provided in Additional file 1.

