### Participants

#### Inclusion criteria

A total of 180 patients will be recruited from the outpatient clinics of the two hospitals. The eligibility criteria for the study include: 1) those with a diagnosis of psoriasis vulgaris (referring to the 2008 clinical guidelines of psoriasis reported by the Chinese Medical Association [31]; 2) aged 18 to 70 years; 3) psoriasis vulgaris patients (Psoriasis Area and Severity Index score (PASI) score of 7–20, with body surface area (BSA) affected < 30%); and 4) willing to sign a written informed consent.

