### Randomization

Eligible patients will be randomly assigned in a 1:1 ratio to one of the two groups (the treatment group who receive auricular acupressure plus calcipotriol betamethasone ointment or the control group who receive calcipotriol betamethasone ointment) at the second visit through central randomization. Equal randomization will be conducted using a computer-generated random allocation sequence through the stratified block randomization method of the SAS software (version 9.12; SAS Institute, Inc., Cary, NC, USA) with a block size of 4 by the Key Unit of Methodology in Clinical Research (KUMCR) of Guangdong Provincial Hospital of Chinese Medicine. Allocation concealment will be ensured since the randomization code will be released by the Interactive Web Response System for Chinese Medicine Trials (IWRS-CMT), which is a verified online randomization facility established by the KUMCR (http://www.gztcmgcp.net/sjxt /login.asp). Following this, the participants will be randomly allocated to the two different groups. The practitioners will be aware of the allocation arm according to the different medical procedures. However, the evaluation of participants and the analysis of the results will be performed by physician assessors and statisticians who are blinded to the group allocation [32].

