### Outcome

#### Primary outcome measurement

The primary outcome measure in the trial is relapse rate in the treatment period and follow-up period. Relapse is defined as losing 50% of the improvement obtained from treatment once the treatment is stopped [40]. The PASI will be assessed every visit during the treatment period and the follow-up period. Meanwhile, patients will be required to report the emergence of a variety of conditions at any time in the study period. Assessors will evaluate the PASI score on the same or closest day. Target lesions will be recorded as digital photographs by single-lens reflex (SLR) cameras at every visit.

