### Sample size

There is a growing body of research evaluating the effect of auricular acupressure for various diseases. However, there is still a lack of studies evaluating the effect of auricular acupressure on psoriasis. There is no previous study on which to base the sample size calculation. Thus, we used the primary outcome relapse rate to determine a sample size calculation. Based on the study of Menter et al. [42], the relapse rate of calcipotriol betamethasone ointment topical therapy after 4 weeks of treatment and 4 weeks of follow-up is 82%. We assume that the relapse rate of auricular acupressure therapy combined with calcipotriol betamethasone ointment topical therapy for psoriasis in week 12 is 20% less than topical therapy alone and that the relapse rate of calcipotriol betamethasone ointment topical therapy is 82%. On the basis of this hypothesis, and in order to compare the two groups for a significance level α = 0.05 and a power 1 – β = 0.80, we calculated the sample size by PASS statistics software (version 11.0.10; NCSS LLC., Utah, USA); 77 patients with psoriasis would have been required in each group to achieve 80% power to detect a difference between the group proportions of −0.2. The test statistic used is the two-sided *Z* test with pooled variance. The significance level of the test is targeted at 0.05. Considering 15% loss to follow-up, 90 patients are needed in each arm, totaling 180 patients in all.

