### Statistical analysis

All analyses will be performed with PASS Statistics and SAS 9.2 software by a statistician who is blinded to the random allocation of groups. An intent-to-treat (ITT) basis statistical analysis with a 95% confidence interval will be performed using multiple imputations. The major imputation is multiple imputation by chained equations (MICE). The ITT analysis will include all patients who are randomized [43]. Safety analysis will be undertaken by analyzing the frequency of adverse events which are suspected as related to the treatment. Planned subgroup analyses include those based on the type of TCM syndromes and severity of psoriasis. The various parameters observed will be compared using a Chi-square test for noncontinuous variables (i.e., the primary outcome relapse rate) and *t* test and analysis of variance (ANOVA) for continuous variables. In order to distinguish the treatment effect and time effect, the repeated measures ANOVA change from baseline will be performed for the different time point assessments. Statistical significance is established at *P* < 0.05. No formal interim analysis is planned.

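### Two hospitals, but no hospital term in the named strata or the primary chi-square test: the test stays valid, and a little precision is given up

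*Protocol article*

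**What the plan says.** **Sites.** Under Study design the trial is "performed at two clinical research centers in China (Guangdong Provincial Hospital of Chinese Medicine and Guangzhou Red Cross Hospital". Under Inclusion criteria, "A total of 180 patients will be recruited from the outpatient clinics of the two hospitals". No split between the hospitals is given.

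**Strata.** Study design states: "Eligible participants will be stratified by age and sex and randomly allocated in a 1:1 ratio to one of the treatment arms". The Randomization section describes a "computer-generated random allocation sequence through the stratified block randomization method of the SAS software", with blocks of four and central release of the code. It names no factor.

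**Primary test.** Under Statistical analysis, outcomes are to be "compared using a Chi-square test for noncontinuous variables (i.e., the primary outcome relapse rate". The Sample size section uses the matching unstratified form: "The test statistic used is the two-sided *Z* test with pooled variance".

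**Hospital elsewhere.** No analysis in the article uses hospital. The planned subgroups are TCM syndrome type and psoriasis severity.

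**The concern.** Hospital is a plausible source of variation in this outcome. Relapse is a threshold on PASI, which an assessor scores and which the article's own Table 1 says takes experience to score accurately. The two sites may also see different outpatients, although the article does not say so.

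With no hospital stratum, the arms can differ by chance in their share of each hospital. With no hospital term in the test, the estimate is not corrected for that. Analysing by the age and sex strata would not help, because neither stands in for hospital.

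At stake are a chance shift in the observed relapse difference and some precision that a recorded baseline factor could supply.

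**Working it through.** **1. The plan's own figure.** Inputs from Sample size: 82% against 62%, two-sided alpha 0.05, power 0.80, pooled Z test.

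n = [1.960·√(2·0.72·0.28) + 0.842·√(0.82·0.18 + 0.62·0.38)]² / 0.20² = (1.245 + 0.521)² / 0.04 ≈ 78 per arm.

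The article states 77, where power is 0.795. For 15% loss, 77/0.85 gives 91 and 77·1.15 gives 89; the article states 90. The figures reproduce to within two patients.

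**2. Assumptions.** The article gives neither the hospital split nor the hospital difference in relapse. I take a share s of 0.5 or 0.7 for one hospital, a gap of 0, 10, 20 or 30 points, and the same 20-point effect at both hospitals.

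**3. Chance imbalance at 90 per arm.** SD of the between-arm difference in hospital share = √(2s(1−s)/90).

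- s = 0.5: √(0.50/90) = 0.075, so the 95% limit is 1.96·0.0745 = 14.6 points.
- s = 0.7: √(0.42/90) = 0.068, so the limit is 1.96·0.0683 = 13.4 points.

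Shift in the relapse difference = imbalance × gap:

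- 10-point gap: 1.3 to 1.5 points.
- 20-point gap: 2.7 to 2.9 points.
- 30-point gap: 4.0 to 4.4 points.

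**4. How much variance a hospital term could remove.** The average variance per patient over the two arms is (0.82·0.18 + 0.62·0.38)/2 = 0.1916. The between-hospital part is s(1−s)·gap². At s = 0.5 it is 0.0025, 0.0100 and 0.0225 for gaps of 10, 20 and 30 points, which is 1.3%, 5.2% and 11.7% of the total. The total is fixed by the overall rates, so a larger gap does not raise it.

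**5. Power at 77 per arm.** Simulation, 40,000 runs per scenario, allocation not stratified by hospital. CMH is the Cochran-Mantel-Haenszel test by hospital.

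| Split | Gap | Chi-square, % | CMH, % | Change, points |
|---|---|---|---|---|
| 50:50 | 0 | 80.32 | 80.04 | −0.28 |
| 50:50 | 10 | 80.09 | 80.34 | +0.25 |
| 50:50 | 20 | 80.30 | 82.12 | +1.82 |
| 50:50 | 30 | 80.24 | 84.77 | +4.53 |
| 70:30 | 0 | 79.76 | 79.35 | −0.41 |
| 70:30 | 10 | 79.98 | 80.10 | +0.12 |
| 70:30 | 20 | 80.16 | 81.64 | +1.48 |
| 70:30 | 30 | 79.92 | 83.84 | +3.92 |

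The simulation error of each power figure is √(0.8·0.2/40,000) = 0.2 points. A separate set of 20,000 runs at 50:50 agrees: 0.804 to 0.807, 0.806 to 0.822 and 0.797 to 0.844 for gaps of 10, 20 and 30 points.

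**6. Type I error.** For the planned chi-square test without hospital strata it is 0.051 to 0.054 in all eight scenarios.

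**7. Stratifying the randomisation as well.** At 50:50, CMH power is then 82.14% (gap 20) and 85.20% (gap 30), against 82.12% and 84.77% with adjustment in the analysis alone. Adjustment recovers almost all of the gain.

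**The case against.** A reader might infer three stronger points, and the documents support none of them.

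- **That hospital variation widens the error bars and erodes the 80% power.** It does not. The variance of the pooled comparison depends on the overall relapse rates, and chi-square power stays near 80% at every gap. Power is forgone relative to a better test, not lost relative to the plan.
- **That different rating habits could pass for a treatment effect.** Allocation is central and 1:1, so hospital is unrelated to arm in expectation, and assessors are blinded. Only the chance shift in step 3 remains, and the ordinary 95% confidence interval already allows for it. Moreover, "Relapse is defined as losing 50% of the improvement obtained from treatment once the treatment is stopped" is a relative change within the patient, so a proportional rating difference between hospitals largely cancels.
- **That differences between therapists are part of the problem.** Therapists treat only one arm. A therapist difference between hospitals would be a hospital-by-treatment interaction, which a hospital main effect or a CMH test does not remove.

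Two further objections have weight. First, the size depends on unknown gaps. A 30-point gap at 50:50 means 97% against 67% relapse among controls and 77% against 47% in the acupressure arm, which is extreme for sites sharing eligibility limits, ointment and therapist training. Second, centre adjustment is often settled in an analysis plan, and CMH is itself a chi-square-type test, so the article's wording does not exclude it. Against that, the article does not leave the matter open: it lists the strata and names the test, and it sizes the trial on an unstratified test.

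**Conclusion.** The point holds as one of efficiency. Hospital is in neither the named strata nor the named primary test. The test remains valid, the stated power stands and the sample size does not change.

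The size rests wholly on the assumed split and gap. The chance shift is 1.3 to 4.4 points at the 95% limit. The power gain from hospital adjustment is about 0 to 0.4 points at a 10-point gap, 1.5 to 2 at 20 and 4 to 5 at 30. If the hospitals do not differ at all, adjustment costs about 0.3 to 0.4 points. I rate this a free improvement, optional in priority.

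**What to change.** Before unblinding, name as the primary test either a Cochran-Mantel-Haenszel test or a logistic model, adjusted for hospital together with the randomisation strata of age and sex. Hospital alone would leave out the factors actually used to randomise. The article gives no age bands; if crossing them with sex and hospital makes the CMH strata thin, the logistic model with main effects is the safer choice.

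Report the adjusted risk difference with its 95% confidence interval. Include hospital in the imputation model and the continuous-outcome models, and tabulate relapse by arm within each hospital. That table is also where any difference in effect between hospitals would show.

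Leave the randomisation unchanged. With 154 of 180 patients recruited, only 26 remained, and step 7 shows that adjustment in the analysis is enough.

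The cost is one line of analysis wording and a few degrees of freedom, one of them for hospital. No patients, visits or data are added. Fixing it while the statistician is still blinded keeps the adjustment from looking post hoc.

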**Fig. 2 Fig2:**
[figure not shown]
Flowchart of the study

### Participants

#### Inclusion criteria

A total of 180 patients will be recruited from the outpatient clinics of the two hospitals. The eligibility criteria for the study include: 1) those with a diagnosis of psoriasis vulgaris (referring to the 2008 clinical guidelines of psoriasis reported by the Chinese Medical Association [31]; 2) aged 18 to 70 years; 3) psoriasis vulgaris patients (Psoriasis Area and Severity Index score (PASI) score of 7–20, with body surface area (BSA) affected < 30%); and 4) willing to sign a written informed consent.

#### Exclusion criteria

Participants will be excluded if they are experiencing or have a history of the following: 1) psoriatic arthritis, guttate psoriasis, inverse psoriasis or exclusively involving the face; 2) pregnancy, breast-feeding, or those who intend to become pregnant within 1 year; 3) a Self-rating Anxiety Scale (SAS) > 50 or Self-rating Depression Scale (SDS) > 53, or with other psychiatric disorders; 4) important systemic disease that cannot be controlled through common treatment (either with infection, electrolyte imbalance, acid-base disturbance, calcium metabolic disorder, or cancer; 5) those allergic to any medicine or ingredients used in this study; 6) those participating in other clinical trials or those who have participated within 1 month before entry into the study; 7) those who have been treated with topical treatments (i.e., corticosteroids, retinoic acid) within 2 weeks, or systemic therapy or phototherapy (ultraviolet B) and psoralen combined with ultraviolet A within 4 weeks, or biological therapy within 12 weeks before beginning the study.

### Randomization

Eligible patients will be randomly assigned in a 1:1 ratio to one of the two groups (the treatment group who receive auricular acupressure plus calcipotriol betamethasone ointment or the control group who receive calcipotriol betamethasone ointment) at the second visit through central randomization. Equal randomization will be conducted using a computer-generated random allocation sequence through the stratified block randomization method of the SAS software (version 9.12; SAS Institute, Inc., Cary, NC, USA) with a block size of 4 by the Key Unit of Methodology in Clinical Research (KUMCR) of Guangdong Provincial Hospital of Chinese Medicine. Allocation concealment will be ensured since the randomization code will be released by the Interactive Web Response System for Chinese Medicine Trials (IWRS-CMT), which is a verified online randomization facility established by the KUMCR (http://www.gztcmgcp.net/sjxt /login.asp). Following this, the participants will be randomly allocated to the two different groups. The practitioners will be aware of the allocation arm according to the different medical procedures. However, the evaluation of participants and the analysis of the results will be performed by physician assessors and statisticians who are blinded to the group allocation [32].

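### A fixed block size of 4, with practitioners aware of the arm, leaves up to one third of allocations open to deduction, so web release alone does not secure concealment

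*Protocol article*

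**What the plan says.** All of this is in the protocol article.

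- **Block size and ratio (Randomization).** The sequence is stratified and blocked, "with a block size of 4 by the Key Unit of Methodology in Clinical Research (KUMCR) of Guangdong Provincial Hospital of Chinese Medicine". Allocation is equal: "Eligible patients will be randomly assigned in a 1:1 ratio to one of the two groups". One block length is given, with no mention of variation.
- **Timing (Randomization).** Allocation takes place "at the second visit through central randomization".
- **Who knows the arm (Randomization).** "The practitioners will be aware of the allocation arm according to the different medical procedures". Assessors and statisticians are blinded.
- **Concealment (Randomization).** "Allocation concealment will be ensured since the randomization code will be released by the Interactive Web Response System".
- **Strata (Study design).** "Eligible participants will be stratified by age and sex and randomly allocated in a 1:1 ratio". Two hospitals take part. Centre is not named as a stratum, and the age bands are not given.
- **Progress (Trial status).** 154 patients had been recruited, against a target of 180.

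The article does not say who enrols patients, whether those people also treat, or whether the block size was withheld from the sites.

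**The concern.** The protocol gives web release as the reason that concealment is assured. That reason covers only one of two routes to the next allocation. Web release stops anyone reading the list. It does nothing about deduction: in a block of two plus two, two patients in the same arm fix the next two, and any three patients fix the fourth. Past allocations are visible, because one arm wears seeds on both ears for five days after each weekly session (Auricular acupressure treatment), and the next patient's sex and age are known before randomisation.

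What is at stake is selection before allocation. Since randomisation waits until the second visit, someone who foresees the arm has time to bring forward, delay or decline a patient. Relapse is defined on PASI (Primary outcome measurement), the stated test of the primary outcome is a Chi-square test (Statistical analysis), and no baseline adjustment is stated. Blinded assessment and intention-to-treat analysis both act after allocation and cannot undo selection that came before it.

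**Working it through.** The protocol gives no predictability figure, so there is none to reproduce.

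**Inputs.** Block size 4 and ratio 1:1 (Randomization); strata age and sex, two centres (Study design); N = 180 (Sample size); 154 recruited (Trial status). The number of strata, the centres' shares of recruitment and what recruiting staff can see are not given. They are assumptions below.

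**1. Full knowledge, complete blocks.** A 2 + 2 block has 6 equally likely orders. The observer knows the block size, where the block starts, and every earlier allocation in it.

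| Position | Probability that the allocation is certain | Probability that the best guess is right |
|---|---|---|
| 1 | 0 | 1/2 |
| 2 | 0 | 2/3 |
| 3 | 1/3 (first two in the same arm) | 2/3 |
| 4 | 1 | 1 |

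- Certain: (0 + 0 + 1/3 + 1)/4 = 33.3%.
- Best guess: (0.5 + 0.667 + 0.667 + 1)/4 = 70.8%, against 50% by chance.
- Over 180 patients: 180 × 1/3 = 60 deducible allocations at most.

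**2. Incomplete last blocks.** Simulating N = 180 with fixed blocks of 4 and full knowledge, the certain share is 32.4% with 4 strata, 31.6% with 8 and 30.6% with 12. Stratification alone hardly lowers the ceiling for someone who tracks every stratum.

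**3. One list shared by two centres.** The observer sees only their own centre's patients and guesses whichever arm has had fewer of them so far in that stratum. The proportion guessed right, by simulation:

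| Own centre's share of patients | 1 stratum | 4 strata |
|---|---|---|
| 50% | 52.8% | 54.7% |
| 70% | 53.9% | 56.8% |
| 90% | 57.0% | 61.5% |
| 100% | 70.9% | 70.5% |

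This is a simple rule and not necessarily the best one available, so these figures are indicative. If lists were in fact kept per centre, the certain share returns to about 31–33%.

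**4. Random block lengths.** Even an observer who knows the set of lengths, but not each block's length, loses nearly all certainty. The ranges are over 1, 4 and 8 strata.

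| Lengths | Certain | Best guess right |
|---|---|---|
| 4 only | about 32–33% | about 70–71% |
| 4 or 6 | about 5–6% | about 69% |
| 4, 6 or 8 | about 2% | about 67–68% |

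**5. Which check would show selection.** Suppose that steering puts milder patients in one arm and more severe patients in the other whenever the allocation is deducible. I assumed a PASI standard deviation of 3 and a 3-point gap between arms in every deducible allocation, with 180 patients. Comparing deducible with non-deducible patients is then significant in about 6% of simulated trials, close to the 5% expected by chance, because the opposite shifts cancel. Comparing the arms within the deducible allocations is significant in about 96%.

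**The case against.** The strongest reply is that central web release is a recognised way to conceal allocation and that the one-third figure needs more knowledge than the protocol gives anyone. Several stronger readings are tempting, and the text does not support them.

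- **That recruiters foresee a third of allocations.** The article says that practitioners know the arm. It does not say that they recruit, or that recruiters see earlier allocations in order. With no centre stratum, one hospital sees only part of each block.
- **That the concealment claim fails outright.** The list is hidden. Only deduction remains, and whether anyone could use it is unknown.
- **That recruiters knew the block size because it is in print.** The article appeared with 154 patients already recruited, so disclosure through it could touch at most 180 − 154 = 26. What the full protocol told the sites cannot be seen.
- **That generation by a unit of the lead hospital is itself a leak.** The text describes a methodology unit and gives recruiters no access to its list.
- **That the relapse comparison is biased.** No such effect has been estimated. SAS and SDS are self-rated, participants are evaluated by blinded assessors, and relapse is measured against each patient's own improvement. All three limit the room to steer at the eligibility thresholds.

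These points set the size of the concern without removing it. None of them closes the deduction route. Delaying or declining a patient at the second visit needs no change to any score. The stated reason for concealment still covers less than the sentence claims.

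**Conclusion.** The point holds in a limited form. A single fixed block of 4, with practitioners aware of the arm, makes up to one third of allocations deducible (33.3% certain, best guess right 70.8% of the time). That ceiling requires staff who know the block size and see every earlier allocation in an age-by-sex stratum. On the literal reading of one list shared by two centres, a one-centre observer using a simple rule does modestly better than chance, at about 53–62%. Concealment is not fully secured against deduction, and web release alone does not ensure it. The document gives no sign that selection took place. The change is worth making because it is cheap and because a suitable table would let readers judge whether selection occurred.

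**What to change.** 1. **Patients still to be randomised (at most 26 at publication).** Have the methodology unit issue the rest of the sequence in randomly varying block lengths that are not disclosed to recruiting staff at either hospital. Start once part-filled blocks have been completed or closed. Certain predictions fall to about 2–6%. The best-guess rate falls only to about 67–69%, so the gain is mainly in removing certainty.
2. **Wording.** In place of the statement that concealment is ensured, say that the code is concealed by central web release and that block lengths are withheld from recruiting staff. State also whether each list is shared by the two centres or kept per centre.
3. **Patients already randomised.** Flag the allocations that were deducible from the earlier ones in their block. Within that set, compare baseline PASI between patients assigned to acupressure and those assigned to control, and report it beside the primary result. Do not pool the deducible patients and compare them with the rest, since opposite steering would cancel.

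**Cost.** A protocol change in an ongoing trial, a regenerated remainder of the list, one extra table, and a slightly larger possible imbalance within strata. The first step reaches few patients, so most of the value lies in the third.
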